### Participant timeline

Participants will complete a baseline questionnaire following consent and prior to the randomisation at week zero. Within three weeks of randomisation, an occupational therapy glove fitting appointment will be arranged to ensure there is sufficient length of time to wear the gloves prior to the 12-week follow-up. Two to four weeks after glove fitting (dependent on each departments’ usual practice), participants will attend an occupational therapy review appointment, either in person or by telephone, as per departmental policy. Participants will receive the follow-up questionnaire at 12-week following the date of baseline questionnaire completion. (See Figs. 1 and 2).

**Fig. 1 Fig1:**
[figure not shown]
A-GLOVES trial: flow of participants

**Fig. 2 Fig2:**
[figure not shown]
SPIRIT flowchart: schedule of enrolment, interventions and assessments

#### Data collection

The baseline questionnaire includes: demographic factors i.e. age, gender, living situation, number of dependents living with them, and employment status; and condition specific factors, i.e. duration of their symptoms, time since diagnosis, current medication regimen and whether they have had a steroid injection/started on oral steroids within the last six weeks.

Both the baseline and the 12-week follow-up questionnaire include:

The primary outcome:Hand pain: measured on a numeric rating scale (NRS) of hand pain in the dominant hand during the day when doing moderate hand activities. The anchor points are no pain (0) to severe pain (10). The pain NRS is a widely-used outcome measure in RA clinical trials. During development and psychometric testing of a patient-reported outcome measure, it was identified that participants had a strong preference for completing NRS over visual analogue scales. This study also identified test-retest reliability of pain (on movement and at rest) were between r_s_ = 0.70 to 0.72. The pain NRSs had significant correlations (*p* < 0.001) with SF36v2 Bodily Pain scales (r_s_ -0.69 to -0.77) [21] (Table 1).And secondary outcomes including:Stiffness: measured through a) Patient self-reported duration of early morning stiffness affecting the hands (hours/minutes); b) 0-10 point numeric rating scale of hand stiffness (with anchor points of no (0) and severe (10) hand stiffness) - separately for the dominant and non-dominant hands.Self-reported hand condition: a five-point rating scale of very severe/severe/moderate/good/very good.Hand function: measured by the Measure of Activity Performance in the Hand (Map-HAND), which has been shown to be unidimensional and have good reliability and validity in a British RA population [22, 23] and the Michigan Health Questionnaire (MHQ), which assesses for the right and left hands separately: physical status of the hand (movement, strength sensation: 5 items); daily activities performed with the hands/arms (5 right and left; 7 bilateral); impact of their condition on their normal activities (5 items); pain frequency, severity and impact (5 items); perceived appearance of their hands (4 items); satisfaction with hand abilities (6 items) and also has good reliability and validity [24, 25].Disability: the Health Assessment Questionnaire (24 items of daily function) [26]Health-related quality of life (HRQoL) is measured using the standardised five-item EuroQoL, 3-level version (EQ-5D-3 L) [27, 28], which is recommended by National Institute of Health and Clinical Excellence (NICE) for economic evaluations in clinical trials and has proven responsiveness, reliability, and validity in trials of interventions for RA [29, 30].

The outcome measures within the baseline and 12-week questionnaire are also listed in Table 1.

#### Patient interviews

At 14 weeks, participants (*n* = 10–15 from each group) will be purposively selected to participate in a semi-structured, face-to-face or telephone interview to investigate their views on: benefits or negative effects of glove wear (including when at work for those who are employed); glove appearance, quality, comfort, ease of applying; and willingness to buy gloves in future. Purposive sampling will be based on: 1:3 male to female ratio (as per the distribution of RA in population), and a range of ages, baseline hand pain (mild/moderate/or severe) and 12-week self-reported levels of adherence with glove wear. The semi-structured interview schedule is outlined in Table 2.

**Table 2 Tab2:** A-GLOVES semi-structured qualitative interview schedule

A-GLOVES Trial: Qualitative Semi-structured Interview Schedule	
Opening/Main Question	
“Having worn the arthritis gloves for up to 12 weeks, could you tell me about any negative or positive effects these have had on your hand pain and hand problems?”	
The following prompts may be used to expand on the answers given:	
1	What effect did they have on your hand pain, hand stiffness and ability to use your hands?
2	Were there any particular activities you found they helped with? [For example: personal care; household activities; leisure/social activities; driving; work].
3	Were there any particular activities you found they did not help with? [For example: personal care; household activities; leisure/social activities; driving; work].
4	How did you find wearing them?
5	How was it to put them on and off your hands?
6	Was there anything about the gloves or their effects which you think helped/hindered your hand pain and hand problems?
7	If they were helpful: when did you find them helpful to wear: either in the day or at night (or both)?
8	If they were not helpful: when did you find them unhelpful to wear: either in the day or at night (or both)?
9	For those employed: Have you used them at work? If yes, were they helpful? And in what ways? If not helpful, why was this?
10	Did you have any problems wearing the gloves?
11	What did you think of the gloves appearance?
12	What did you think of the quality of the gloves you were given?
13	How did you find cleaning them?
14	Would you consider buying them in the future?
15	Would you change anything about them to make it better for your use? (e.g. colour, texture, amount of pressure applied, size, length)

All interviews will be audio recorded, transcribed verbatim and thematically analysed by three researchers to increase the validity of findings.

### Sample size

This was calculated using data from the feasibility study. Minimal clinically important differences for pain scales in RA are estimated as 1.1 points on a 0–10 scale [31, 32]. The mean change in hand pain score during activity (measured four weeks post-intervention) was -1.03 (SD 2.22). As the SD from the feasibility data might be an underestimate, the 80% upper one-sided confidence limit of the estimated SD, i.e. 2.48 was used. To identify a 1.1 point difference, SD = 2.48, p = 0.05 and 80% power, 80 participants are required per group. Allowing for a 20% attrition (i.e. non-return of 12 week questionnaire and a small number (up to 2%) not receiving a glove for their dominant hand (because they only require a glove for their non-dominant hand, and therefore not providing primary outcome data), we intend to recruit 205 participants.

### Recruitment

At each participating site a Principal Investigator (PI) (senior occupational therapist/consultant rheumatologist) will be identified, to be responsible for identification, recruitment, consent and provision of baseline questionnaires, along with adherence to the study and treatment protocols, following Good Clinical Practice Guidelines.

Members of the health care team and occupational therapists at participating sites will identify adult patients with RA or IA and persistent hand pain during the patients’ Rheumatology, occupational therapy or hand therapy appointment. Either a research facilitator or occupational therapist will then screen patients for eligibility using the A-Gloves Trial Eligibility Screening Form. (See Fig. 3 for recruitment procedure). All eligible patients will be provided with a study explanation and information pack. (See Additional file 1).

**Fig. 3 Fig3:**
[figure not shown]
Recruitment and consent flowchart: rheumatology clinic/occupational therapy

If a site is encountering difficulty screening sufficient numbers in clinics, then potential participants will be identified from medical or occupational therapy records by members of the health care team. The patient will then be mailed a Study Information Pack by the research facilitator or occupational therapist. (See Fig. 4 for recruitment procedure).

**Fig. 4 Fig4:**
[figure not shown]
Recruitment flowchart via medical/OT records/health care staff and study information pack mailed/provided to patient

At the screening stage, participants identified as having had a steroid injection or started oral steroids in the last six weeks, but who otherwise meet the inclusion criteria, will not be consented but will be re-screened six weeks after the date of steroid injection/starting oral steroids to re-check trial eligibility. Steroids can reduce hand pain and thus would be a confounding factor in evaluating glove effectiveness. If at six weeks they are still eligible, they will be re-approached for consent.

Participants may receive a steroid injection or start oral steroids following consent. If this occurs between consent and glove fitting, the occupational therapist will identify this at the glove fitting appointment and defer glove fitting for six weeks from the date of injection/steroid start. It is not anticipated that this will be a common event. If the participant starts steroids following glove provision and their hands are still symptomatic, they will be advised to continue glove wear as prescribed, as this is a pragmatic trial. If the patient reports that their hands are no longer causing them pain or discomfort they will be advised not to wear the gloves. However, they will remain in the trial and complete the 12-week questionnaire, as we will be conducting an intention to treat analysis.

Following consent, by the research facilitator or occupational therapist, participants will be provided with a baseline (i.e. 0 weeks) questionnaire to complete and return in a Freepost envelope to the trial manager. On receipt of the completed questionnaire, the trial manager will enter their details into a web-based MACRO database (managed by Lancashire Clinical Trials Unit [CTU]) and request that the unblinded CTU staff perform the assignment of the intervention.

### Assignment of intervention

#### Allocation and sequence generation

Participants will be randomly assigned to either the intervention or placebo glove group with a 1:1 allocation generated and delivered by ‘Sealed Envelope,’ an online, central randomisation service (www.sealedenvelope.com). The randomisation schedule will be stratified by whether or not the participant has had a change in or received new medication (specifically DMARDs or biologics) within the last three months, using permuted blocks of random sizes.

#### Concealment mechanism

The block sizes or schedule will not be disclosed to the trial manager, occupational therapists or research facilitators to ensure concealment. Randomisation will occur only once the trial manager confirms a participant’s eligibility, consent and that they have completed the baseline questionnaire.

#### Implementation

Within three working days of notification by the trial manager, unblinded CTU staff will perform the randomisation and securely e-mail a referral for either intervention or placebo gloves to the relevant site. Within three weeks of referral, the occupational therapist will make an appointment and provide the participant with the appropriate gloves.

### Blinding

Due to the nature of the intervention it will not be possible for therapists to be blinded to group allocation. As most sites will only have one Rheumatology occupational therapist, both intervention and placebo gloves will commonly be provided by the same occupational therapist. During the glove training and site monitoring visits, the importance will be emphasised of not divulging to the participant whether they are receiving an intervention (arthritis glove) or a placebo glove. Therapists will be asked not to use the term “compression” glove (an alternative name for arthritis gloves in clinical practice) in any participant interaction, as this may unblind patients as to whether they are receiving an intervention or placebo glove. Participants will be kept blinded to group allocation by describing the study throughout as a comparison of two types of arthritis glove and not divulging the differences between these.

The trial manager will remain blinded to group allocation until the participant has completed and returned their 12-week questionnaire and the data been verified at the CTU. The trial manager will then be unblinded to group allocation for some participants in order to complete interviews with participants (*n* = 24–30).

Data co-ordination and data entry staff at the CTU, responsible for baseline and 12 weeks questionnaires management, will be blinded to group allocation. However, data entry for the Treatment Records (which identify the group allocation) will be conducted separately by the CTU Trial Management Team only, to avoid other CTU staff becoming unblinded. Statisticians and the health economist will be blinded to group allocation until analysis is complete.

#### Emergency unblinding

Not applicable as serious adverse events are not known to occur in clinical practice.

### Data collection methods

Outcomes will be collected via self-reported questionnaires at baseline (i.e. prior to randomisation) and 12 weeks later. Glove provision will usually occur within three weeks of randomisation and referral to occupational therapy. Thus, at follow-up, most participants will have worn gloves for about nine weeks. Feedback from glove users indicates that they normally experience any benefits within a short-time of commencing glove-wear.

The trial manager (baseline) and CTU (12 weeks) will monitor return of all questionnaires and the quality of data.
**At 1 week** after questionnaire provision/mailing, if the questionnaire is not yet returned, the trial manager [baseline questionnaire] or CTU [12-week questionnaire] will telephone/text/e-mail (as applicable) to remind the participant to return their questionnaire.
**At 2 weeks** after questionnaire provision/mailing, if the questionnaire is not yet returned, the trial manager [baseline questionnaire] or CTU [12-week questionnaire] will mail a reminder letter and a further copy of the relevant questionnaire (with Freepost envelope).
**If the 12 week questionnaire is not returned by week 16,** the CTU will inform the trial manager who will then telephone the participant to obtain a minimal data set (i.e. at least dominant hand pain during moderate activity and if gloves are being worn (yes/no)). If possible, as much of the following will also be collected: dominant hand pain at night; hand stiffness; MAPHAND; hand condition severity scale; how their hands are in comparison to 12 weeks ago, i.e. before receiving gloves (much better/better/no change/worse/much worse). The trial manager will complete the minimal dataset on a 12-week questionnaire (with participant’s PIN included), identifying on the front page that it is a minimal dataset completed by telephone. If the trial manager is unable to obtain this data, this will be recorded in the Trial Database and data entered as missing.

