**Methods:**

Participants aged 18 years and over with RA or IA and persistent hand pain will be recruited from National Health Service Trusts in the United Kingdom. Following consent, participants will complete a questionnaire booklet, then be randomly allocated to receive intervention or placebo arthritis gloves. Within three weeks, they will be fitted with the allocated gloves by clinical specialist rheumatology occupational therapists. Twelve weeks (i.e. the primary endpoint) after completing the baseline questionnaire, participants will complete a second questionnaire, including the same measures plus additional questions to explore adherence, benefits and problems with glove-wear. A sub-sample of participants from each group will be interviewed at the end of their participation to explore their views of the gloves received. The clinical effectiveness and cost-effectiveness of the intervention, compared to placebo gloves, will be evaluated over 12 weeks. The primary outcome measure is hand pain during activity. Qualitative interviews will be thematically analysed.

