#### Adherence

Recommendations for when to wear gloves will be based on individual needs; most, but not all, patients will be provided with gloves for both hands. Most people experience hand pain during the day and are recommended to wear gloves during activity. Those experiencing hand pain at night, which interferes with sleep, will also be recommended to wear gloves at night. Gloves are not recommended to be worn continually. All participants will receive written information about glove wear and care, using the sample information sheet in the A-Gloves Occupational Therapy Glove Provision Manual [17].

To check for correct glove fit and any problems, occupational therapists will either: within two to four weeks of glove provision offer a review appointment (in person or by telephone); or ask the participant to get in contact if experiencing problems, if this is their normal departmental policy. At the review appointment, participants will be reminded about their glove wear regimen and the need to continue to wear the gloves until the 12-week follow-up questionnaire is completed. At the end of their trial participation, they will be contacted with further instructions about future glove wear.

Adherence to glove wear will be assessed in the 12-week follow-up questionnaires, by asking participants to describe their glove wear for right and left hand gloves. This will include, over the last four weeks, the: average time worn during the day and/or at night; and the average number of days per week gloves were worn. The participant will also be asked to state whether they have obtained arthritis gloves from elsewhere (if they did so, as it is possible for patients to purchase gloves in shops and on-line) and glove wear related to these (if applicable).

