#### Concomitant care

Occupational therapists are asked not to provide resting, wrist, finger or thumb splints or any other occupational therapy interventions (apart from joint protection and hand exercises) to participants whilst they are in the trial (i.e. during their 12 weeks participation). However, participants are permitted to attend Physiotherapy for lower limb interventions if required. Data on participants’ use of concomitant care is collected via the 12-week questionnaire.

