	If yes, what type these were			✓
	How their hands are in comparison to 12 weeks ago, i.e. before receiving gloves	(much better/better/no change/worse/much worse)		✓
	Concurrent use of any resting, wrist, finger or thumb splints			✓
	Adherence to glove wear	During the day and at night for right/left hand gloves; average time worn at night/during the day; average number of days per week gloves have been worn		✓
	Whether participants considered gloves provided any benefit	Yes/No		✓
	Whether they will continue to wear the gloves provided	Yes/No		✓
	If they considered the gloves of any benefit, what were these			✓
	Any problems encountered when wearing gloves	Freetext		✓

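### The fixed 12-week look-back items stop matching the trial's own reference points for participants who answer late, above all those telephoned from week 16

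*Protocol article*

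**What the plan says.** **Timing of the outcome.** The abstract fixes the endpoint: "Twelve weeks (i.e. the primary endpoint) after completing the baseline questionnaire, participants will complete a second questionnaire". Participant timeline starts the clock at the same point: "Participants will receive the follow-up questionnaire at 12-week following the date of baseline questionnaire completion". Under Data collection methods, reminders follow one and two weeks after mailing, the second with a fresh copy of the questionnaire. The next step is conditional: "If the 12 week questionnaire is not returned by week 16". The trial manager then telephones for a minimal set, "at least dominant hand pain during moderate activity and if gloves are being worn (yes/no", and, if possible, some further items. One of these is "how their hands are in comparison to 12 weeks ago, i.e. before receiving gloves (much better/better/no change/worse/much worse".

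**Look-back items.** Table 1 (Outcomes) words the change item the same way for the paper form: "How their hands are in comparison to 12 weeks ago, i.e. before receiving gloves". It also asks about steroids started, and other upper-limb therapy received, over the preceding 12 weeks. Statistical methods plans a sensitivity analysis that excludes anyone who received steroids from randomisation until the outcome was measured.

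**Treatment limits and glove wear.** Concomitant care asks therapists not to provide splints or most other occupational therapy "to participants whilst they are in the trial (i.e. during their 12 weeks participation"). Additional Interventions restricts joint protection and exercise input for the 12 weeks. Adherence sets a different end point for the gloves, since participants are reminded of "the need to continue to wear the gloves until the 12-week follow-up questionnaire is completed".

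**The concern.** The questionnaire items assume that everyone answers at week 12. The follow-up procedure allows later answers and, for persistent non-returners, seeks them only from week 16. A look-back of fixed length moves forward with the date of answering, while the events it should reach (glove receipt, randomisation) stay where they are.

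Three things are at stake. The global change rating may be answered against the wrong reference time. The steroid exclusion cannot be applied uniformly, because late responders are not asked about the whole period that it covers. And for an outcome taken at week 16 or later, the document is unclear about which limits on other hand treatment still apply, because its sections use different end points. Those affected are late responders, who selected themselves into that group.

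**Working it through.** All times are in weeks from completion of the baseline questionnaire.

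**Inputs**
- Endpoint at week 12 (Abstract; Participant timeline).
- Telephone collection from week 16 (Data collection methods).
- Fitting no later than three weeks after randomisation (Participant timeline).
- Randomisation within three working days of notification (Implementation), so 3/5 = 0.6 working weeks.
- About nine weeks of wear expected at follow-up (Data collection methods).

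**The plan's own figure.** Wear at follow-up = 12 − 3 = 9 weeks. This reproduces, and it places expected fitting at about week 3. Adding the randomisation delay gives 3 + 0.6 = 3.6. Postal time for the baseline questionnaire is not stated and is ignored here.

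**Change item.** For an answer at week t, twelve weeks ago is week t − 12. The wording is consistent only if t − 12 falls before the fitting week f, that is, t < 12 + f.

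| Answer week t | t − 12 | f = 1 | f = 3 | f = 3.6 | f = 6 |
|---|---|---|---|---|---|
| 12 | 0 | consistent | consistent | consistent | consistent |
| 14 | 2 | conflict | consistent | consistent | consistent |
| 16 | 4 | conflict | conflict | conflict | consistent |
| 18 | 6 | conflict | conflict | conflict | conflict |

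At the earliest telephone call the two halves of the item differ by 4 − 3 = 1 week for fitting at week 3, and by more for earlier fitting or a later call. Time since fitting is then 16 − 3 = 13 weeks rather than 9.

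**Steroid item on paper.** The item covers weeks t − 12 to t. The exclusion needs randomisation to t. The Recruitment section says the therapist will identify steroid starts between consent and fitting at the fitting appointment, so the uncovered stretch runs from f to t − 12:
- t = 16, f = 3: 4 − 3 = 1 week.
- t = 16, f = 1: 4 − 1 = 3 weeks.
- t = 18, f = 3: 6 − 3 = 3 weeks.
- t = 14, f = 3: week 2 precedes fitting, so no gap.

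This assumes that the finding at fitting is recorded and reaches the analysis.

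**Steroids by telephone.** The listed items are pain during activity, glove wear, night pain, stiffness, the hand-activity measure, hand condition and the change item. Neither steroids nor other hand treatment is among them. For a week-16 call after fitting at week 3, the call therefore supplies nothing for 16 − 3 = 13 weeks.

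**End points side by side.** Limits on other treatment: 12 weeks. Glove wear: until the questionnaire is completed. Primary outcome by telephone: week 16 or later. From week 12 to the call is at least 16 − 12 = 4 weeks, during which the glove instruction still applies but the treatment limits, read literally, do not.

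**The case against.** **The change item is a minor outcome and states its own anchor.** It is listed among the additional outcomes, is sought by telephone only if possible, and says explicitly that the time before gloves is meant. The primary pain score has no 12-week look-back. All this stands and is the main reason the point is minor. The conflict is also not universal: fitting after week 4, for instance after a steroid deferral, keeps the wording true for a week-16 call.

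**Steroid starts are caught at fitting.** This largely stands for early starts, as the one-week residual shows. It does not close the gap, and it does not help with starts after fitting in telephone cases. The call is entered on a 12-week questionnaire form, so the steroid item is on the page, but it is not among the items to be sought.

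**Stronger readings that the document does not support.**
- A reader might infer that late outcomes dilute the treatment effect by a calculable amount. That would need a rescue rate and an effect in late cases, and the document gives neither. The 20% attrition allowance (205 × 0.20 = 41 people) plans for missing data; it is not a count of telephone cases. Gloves are meant to stay in use until the questionnaire is completed, so assuming no effect in late cases has no basis.
- A reader might infer that care becomes unrestricted in week 13. Nothing says that such care starts then. Additional Interventions notes that behavioural programmes are mostly not offered or have waiting lists, and any later care is open to both arms.
- A reader might fault the absence of a latest acceptable date. That may be in the analysis plan or data management plan, which are not shown.
- A reader might want the call moved forward. The second copy goes out at about week 14, so waiting until week 16 gives it time to come back. A late pain score may also be better than a missing one.

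**Conclusion.** The concern holds in a limited form, as a minor point. For anyone fitted by about week 4, the change item contradicts itself in a call from week 16. The paper steroid item falls short of the exclusion period for late returns, by about one week at week 16 with on-schedule fitting and by more with earlier fitting or later return. The telephone set as listed supplies no data on steroids or other hand treatment. The sections on treatment limits, glove wear and outcome collection use end points that do not agree.

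The figures rest on fitting at about week 3, taken from the protocol's own expectation of wear, and on the check at fitting being recorded. The number of late cases is not given, and the direction of any bias in the primary outcome cannot be determined. The sample size is not affected.

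**What to change.** 1. Reword the change item to refer to the time *just before you were given your gloves*. Participants who could not be fitted but remain in the trial need a different reference, such as their first questionnaire.
2. Reword the steroid item to *since you completed your first questionnaire*. This covers the whole period from randomisation whatever the return date, and the start date that Table 1 already requests allows trimming to randomisation. The other-therapy item can be re-anchored in the same way.
3. Add steroid use and other hand treatment to the listed telephone set.
4. Record the date on which each outcome was given, if the form does not already do so, so that late and telephone data can be identified by timing as well as by the front-page flag.
5. Reconcile Additional Interventions and Concomitant care (12 weeks), Adherence (until the questionnaire is completed) and Data collection methods (telephone collection from week 16). Which treatment rule applies in that interval is for the sponsor to decide.

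The cost is a few words in the questionnaire, a slightly longer call and a clarifying amendment.
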